### Economic evaluation

Among the secondary outcomes of the study, we will investigate the cost-effectiveness of the technological intervention, in case the overall intervention does not yield statistically significant improvements in the other primary and secondary study outcomes. Therefore, cost of illness, budget impact and cost-utility analyses will be performed using the perspective of the National Health Service [42] and in agreement with the ITT principle per the CHEERS statement [43].Cost of illness analysis (COI) will define the value of the resources that are expended or foregone as a result of dementia. The COI will consider separately the perspective of the public health system, the users and the society in order to describe in a more comprehensive manner the real impact of the disease in the study contextBudget impact analysis (BIA) will measure the net cumulative effect of the technological intervention for dementia in the Swedish population. If the intervention can reduce the disease burden, it can also assure a reduction in terms of institutionalizations, number of hospitalization days, drug consumption, caregiver burden, etc.Cost-utility analysis (CUA): defined as the ratio between the cost of the technological intervention and the benefit it produces in terms of the number of years lived in full health by the beneficiaries. The result of the analysis will be an incremental cost per quality-adjusted life year (QALY) gained.

Probabilistic sensitivity analyses (PSA) will also be performed on the health economics models using the software TreeAge Pro 2009. Results from the PSA will also be presented as an acceptability curve, graphically illustrating the probability of the intervention being cost effective over a range of willingness-to-pay values.

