**Discussion:**

This is the first randomized controlled trial exploring the implementation of ICT for people with dementia in a large sample in Sweden and one of the first at the international level. Results hold the potential to inform regional and national policy-makers in Sweden and beyond about the cost-effectiveness of ICT and its impact on caregiver burden.

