The UP-TECH project was a recent study about the impact of new technologies for dementia caregivers, involving care staff, engineers, epidemiologists and health economists, which developed and tested a prototypical ICT solution combined with a case-management intervention in more than 100 households in Italy [19]. UP-TECH used home monitoring kits to monitor adverse and dangerous events (e.g., smoke, water leaks, unexpected opening of doors or windows, prolonged absence from bed) through a wireless network and a control unit that sent alarms to the caregivers via mobile phone [20]. Preliminary results of the UP-TECH study have been promising, and user satisfaction with the solution was high [21]. Another relevant study is the ATTILA trial in England [22]. ATTILA uses assistive technology and telecare (ATT) to support independent living at home for people with dementia. The hypothesis of the study is that people with dementia who receive ATT will be less likely to go into institutional care than those who receive equivalent community services without ATT. Results for this study are not yet available as the study is still ongoing.

The TECH@HOME study builds on the experiences of the UP-TECH study and will test the impact of a newly designed technology to support caregivers of people with dementia who are still living in the community, in terms of effectiveness and cost-effectiveness. We hypothesize that technologies can substitute for some of the time caregivers spend in supervision and monitoring activities for people with dementia. The decreased time is expected to reduce the caregiver burden, and thus result in an overall improvement of quality of life for carers and people with dementia.

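### The Economic evaluation section can be read as running the cost-effectiveness analysis only after a non-significant trial, which conflicts with its unconditional status elsewhere in the protocol

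*Protocol article*

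**What the plan says.** The section Primary and secondary outcomes names cost-effectiveness as the last of seven secondary outcomes and attaches no condition. The Background says the technology will be tested "in terms of effectiveness and cost-effectiveness". The Discussion part of the Abstract expects the results to be able to inform policy-makers "about the cost-effectiveness of ICT and its impact on caregiver burden". Neither statement carries a condition.

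The Economic evaluation section repeats the secondary-outcome status. It then says the team will investigate "the cost-effectiveness of the technological intervention", and adds after a comma: "in case the overall intervention does not yield statistically significant improvements in the other primary and secondary study outcomes". The next sentence begins: "Therefore, cost of illness, budget impact and cost-utility analyses will be performed". No sentence in the section says what happens when the other outcomes do improve. The description of the budget-impact analysis nevertheless reasons from benefit: "If the intervention can reduce the disease burden, it can also assure a reduction in terms of institutionalizations". The same section commits the economic analyses to the intention-to-treat principle and plans a probabilistic sensitivity analysis with an acceptability curve.

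**The concern.** Taken at face value, the clause makes a declared secondary outcome depend on the significance of the trial's other results. That is a poor rule for three reasons.

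- Cost-effectiveness is a matter of estimation. The planned acceptability curve already shows the joint uncertainty in cost and effect, so no significance test is needed to decide whether to produce it.
- The answer would be missing when the kit works, which is when a decision-maker would most want to know what the benefit costs.
- If the evaluation is run only after non-significant results, it is run on data selected for low effect estimates.

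The trigger is also undefined. The clause refers to the other primary and secondary outcomes together and does not say whether one significant improvement cancels the evaluation or all of them are required. With the outcome list saying one thing and the methods section another, the team could run or omit the evaluation after seeing the results and cite the protocol either way.

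**Working it through.** **Reading the sections side by side**

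1. Primary and secondary outcomes: cost-effectiveness is a secondary outcome, unconditionally.
2. Background: the kit is tested for both effectiveness and cost-effectiveness, unconditionally.
3. Economic evaluation, opening sentence: cost-effectiveness is investigated *in case* there is no significant improvement.
4. Economic evaluation, next sentence: *Therefore* makes the three economic analyses follow from item 3.
5. Economic evaluation, budget-impact item: the rationale supposes that the intervention reduces disease burden. If item 3 is a condition, this is the situation in which the analysis would have no stated ground.

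If item 3 is a condition, it conflicts with items 1, 2 and 5. If it is not, the wording does not say what was meant. Either way the sentence needs correcting.

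**Illustration of how often the condition would be met**

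Inputs from Sample size calculation and statistics: SD 20 (taken as h/week), 128 dyads per arm after dropout, effect 1 h/day = 7 h/week, power 0.8, dropout 20%. Assumption: two-sided alpha 0.05, which the document does not state.

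*Reproducing the plan's figure first.* n per arm = 2 × (1.96 + 0.842)² × 20² / 7² = 128.2, rounded up to 129, against the stated 128. Dividing by 0.8 for dropout gives 162 per arm, against the stated 160. Power with 128 per arm is 0.80. A one-sided alpha of 0.05 gives 101 per arm and does not reproduce the plan, so the two-sided assumption is the one that fits.

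*Standard error of the difference.* 20 × √(2/128) = 2.5 h/week.

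*Smallest significant difference.* 1.96 × 2.5 = 4.9 h/week.

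*Probability of a non-significant primary result if the true effect is 7 h/week.* Φ((4.9 − 7)/2.5) = Φ(−0.84) = 0.20.

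If the condition is judged on the primary outcome alone, the evaluation would run in about 20% of such trials and be skipped in about 80%.

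*What any or all does to this figure.* If a single significant improvement in any outcome cancels the evaluation, the primary and every non-economic secondary outcome must be non-significant for it to run, so 20% is an upper limit. If it is cancelled only when all of them improve significantly, a non-significant primary is already enough for it to run, so 20% is a lower limit. The document does not choose between these.

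*Selection on the primary estimate.* Given a non-significant result, the expected estimate is 7 − 2.5 × φ(0.84)/Φ(−0.84) = 7 − 2.5 × 0.280/0.200 = 3.5 h/week. This is a statement about care hours only.

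The standard error is for an unadjusted comparison at one time point. The plan specifies ANCOVA and names changes to months 3 and 12, so these figures are approximate.

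**The case against.** The strongest reply is linguistic. A main clause followed by a comma and *in case* is ordinary English for a precaution: the thing is done anyway, as a safeguard. On that reading the authors mean that the economic analyses are planned because the clinical outcomes may fall short of significance, and *Therefore* fits. The unconditional statements in the outcome list and the Background, the budget-impact text, and a cost-of-illness analysis that describes dementia rather than the kit can all be taken as evidence for this reading. This stands as a real possibility. The word *only* does not appear in the protocol. But neither does *even if* or *regardless*, and the section makes no provision for a successful trial. If a precaution was meant, the same edit is needed to say so.

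Some stronger inferences are tempting and are not supported:

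- *A successful trial will certainly yield no cost-effectiveness result.* This follows from one reading of one clause, not from the document as a whole.
- *The evaluation would run in at most 20% of trials.* That holds only if any single significant improvement cancels it, and with an alpha the document does not state.
- *The economic result would be biased by half.* The fall from 7 to 3.5 h/week concerns care hours. The cost-utility result is a cost per QALY, and how far selection on hours carries over depends on correlations the document does not give.
- *Cost-effectiveness is a main aim.* The aim stated in the Abstract and the Discussion concerns caregiver burden. Cost-effectiveness is a secondary outcome, though one the Background puts next to effectiveness.

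It is also fair to say that the clause leaves the design, the data collection, the sample size and the primary analysis untouched. The point is not, however, a detail left to an analysis plan, because the protocol states the clause explicitly.

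**Conclusion.** The point holds as a contradiction and a badly fixed rule. Read as a condition, the opening sentence of the Economic evaluation section conflicts with the outcome list, the Background and its own budget-impact rationale. It permits a declared secondary outcome to be skipped or run according to the observed results, and its trigger (any outcome or all) is undefined. The precautionary reading prevents the claim that the evaluation would definitely be dropped after a positive trial; it does not remove the need to correct the sentence.

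The figure of about 20% illustrates the conditional reading. It rests on a two-sided alpha of 0.05, SD 20 h/week, 128 dyads per arm, a true effect of 7 h/week and the primary outcome alone as trigger. No size can be put on any bias in cost per QALY. Severity is moderate, and confidence that the sentence needs correcting is greater than confidence about what its authors intended.

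**What to change.** Delete the clause beginning *in case* and the *Therefore* that depends on it. State instead that the cost-of-illness, budget-impact and cost-utility analyses will be done by intention to treat on all randomised dyads, whatever the statistical significance of the primary and other secondary outcomes, with the joint uncertainty in cost and effect reported through the acceptability curve already planned. This also removes the any-or-all question.

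The cost is one edited sentence. No new data are needed to remove the condition: the protocol already has the full RUD and the caregiver EQ-5D-3L in the questionnaire given to dyads in both arms. The edit should be made before outcome data are analysed, because a later change could look driven by the results.

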### Subgroup and secondary analyses

The implementation of a technological intervention can be considered “complex” according to the definition of the UK Medical Research Council [44]. This means that the study researchers need to identify and appraise all the intertwining components which are interacting and determining the outcomes themselves. Therefore, specific subanalyses are planned such as intervention integrity, dyad adherence to the study, and acceptance of the technology by the users. The research group plans to administer a further ad-hoc questionnaire at the end of the trial to both the people with dementia and the caregivers to assess their level of satisfaction with the technologies used. A specific ethical approval for this aspect of the study will be sought in the future.

### Handling of potential study bias

Risk of selection bias will be assessed by looking at the results of the enrollment process. Clinical staff will be instructed about how to explain, in very simple terms, what participation in the trial will entail. This is expected to reduce refusals among those people who are not very familiar with new technology. Considering the high level of “digital” education among the older population in Sweden, even compared to other Western countries, the likelihood of a selection bias should be minimized. The involvement of expert dementia nurses in the study also addresses the need to use research staff with a high level of know-how on how to relate with people with dementia and their families. This is also expected to reduce the dropouts and withdrawals during the study, thus increasing overall retention.

Other mediating and confounding variables might be associated with study outcomes, and these could lead to wrong/false results at the end of the trial. The use of a multidimensional questionnaire and the randomization process are expected to reduce such risks by providing several covariates that will be available for the statistical analyses to ensure the two study arms are comparable under several social, clinical and functional profiles.

Last but not least, the lack of adherence to the technology can constitute a major flaw for the study implementation and results. This risk will be minimized by using a standardized but thorough approach to the training of users (both people with dementia and their caregivers) with technologies, by using a very simple technological device, and by having the possibility to remotely monitor in real time the actual use of the devices. The study coordinator will be able to detect when a person is not using the technology and will promptly react in order to understand (and possibly address) the reasons behind the lack of use.

## Discussion

While the enormous technological progress made in recent years has put technologies, such as mobile devices and smart phones, in the reach of many, innovators in dementia care are just starting to explore the full potential of these developments to transform them into valuable products and services for users. There is indeed a lack of studies that evaluate the effectiveness and cost-effectiveness of these new technologically enriched interventions designed for people with dementia. Previous large-scale evaluations of the impact of telemedicine and telecare, such as the Whole Demonstrator System in the UK [45], did not include people with dementia despite Alzheimer’s disease being one of the most burdensome diseases in Europe [41].

This randomized controlled trial aims to evaluate the effects of new technologies on caregiver burden by reducing the time spent in supervision. The trial builds on previous promising results from the UP-TECH project in Italy [19]. The technologies used in TECH@HOME will include similar, but improved, home monitoring kits potentially leading to a greater impact on caregivers’ living and care conditions. In addition, while the UP-TECH study did not allow the researchers to estimate the impact of the technology as a “stand-alone” intervention (the monitoring kits were only given in combination with case-management support), TECH@HOME will overcome this limitation thanks to the possibility of comparing a group of technology users versus nonusers. Results from this intervention in dementia care in Sweden hold the potential to inform regional and national policy-makers in Sweden and beyond.

### Trial status

The trial started recruiting in March 2016 and the assessments are scheduled to continue until December 2017.

## Abbreviations

ADL: Activities of daily living
ANCOVA: Analysis of covariance
ANOVA: Analysis of variance
ATT: Assistive technology and telecare
BIA: Budget impact analysis
CDR: Clinical dementia rating
CI: Confidence intervals
COI: Cost of illness analysis
CUA: Cost-utility analysis
HADS: Hospital Anxiety and Depression Scale
IADL: Instrumental activities of daily living
INRCA: Italian National Institute of Health and Science on Ageing
ITT: Intention-to-treat
MMSE-SR: Mini Mental State Examination
QALY: Quality-adjusted life year
RCT: Randomized controlled trial
RUD: Resource Utilization in Dementia
SD: Standard deviation
